## Abstract

**Background:**

Depression occurs in up to 50% of patients after stroke and limits rehabilitation and recovery. Mood disorders are also highly prevalent in carers; their mental health intertwined with the physical and mental wellbeing of the person they are caring for. We argue that working with families, rather than patients alone may improve the treatment of depression in both patients and their carers enhancing the mental wellbeing and quality of life of both.

**Methods:**

A single blind cluster randomised controlled trial to evaluate whether families after stroke who are treated with the Depression Recognition and Treatment package (DepReT-Stroke) in addition to treatment as usual (TAU) show improved mental well being compared to those families who receive only TAU. We aim to recruit one hundred and twenty-six families (63 in each group). The DepReT-Stroke intervention will help families to consider the various treatment options for depression, make choices about which are likely to fit best with their lives and support them in the use of self-help therapies (e.g. computerised Cognitive Behavioural Therapy or exercise). An essential component of the DepReT-Stroke package will be to help people adhere to their chosen treatment(s). The primary outcome will be the Mental Component Subscale of the SF-36 assessed at baseline and again six months post intervention. Effectiveness of the intervention will be determined using analysis of co-variance; comparing the mean change in MCS scores from baseline to six months follow-up adjusting for the clustering effects of baseline scores and family. An economic evaluation of the intervention will help us determine whether the intervention represents a cost-effective use of resources.

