### Trial Participants

The study population are families living with stroke that have co-occurring depression in the patient, the carer or both. We will recruit 'families' (defined as a person suffering from stroke and their self declared primary carer) from the Norfolk and Norwich University Hospitals (NNUH) NHS Trust Stroke Register [38].

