#### Sample size

The cluster within this trial is the family (patient and carer). We will need to analyse data from 102 individuals (i.e. 51 families) (approximately 51 individuals in the DepReT-Stroke group and 51 individuals in the TAU group). This will provide 80% power to detect, with a significance level 5%, an overall difference between intervention and TAU of 6 points in the SF-36v2 MCS sub-scale with a standard deviation of the MCS of 12 [57] equivalent to an effect size of 0.5SD. The calculation assumes a clustering effect of scores by family with a ICC of 0.05, and that the analysis would adjust for baseline values, with a baseline-endpoint correlation in MCS scores of 0.5. With an estimated 20% attrition rate, this will require randomising 126 individuals at baseline. We pre-defined 0.5 SD (6 points) difference between intervention and TAU as this effect size is clinically significant difference for stroke patients/carers with depression [58].

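### The abstract sets the recruitment target at 126 families; the sample size section sets it at 126 individuals, which is 63 families, half as many

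*Protocol article*

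**What the plan says.** The abstract of the protocol article (Methods) gives the target in families: "We aim to recruit one hundred and twenty-six families (63 in each group").

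The Sample size section counts individuals. For the analysis it says "We will need to analyse data from 102 individuals (i.e. 51 families"), split as "approximately 51 individuals in the DepReT-Stroke group and 51 individuals in the TAU group". For randomisation it says "With an estimated 20% attrition rate, this will require randomising 126 individuals at baseline".

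The size of a family is fixed in two places. Trial Participants has it "defined as a person suffering from stroke and their self declared primary carer", and Sample size says "The cluster within this trial is the family (patient and carer"). Equating 102 individuals with 51 families uses the same ratio of two people per family.

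**The concern.** The number 126 appears in both places with different units, and the units differ by a factor of two. The two statements therefore describe trials of different size.

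The family is the cluster, so the number of families is the figure that recruitment, randomisation and reporting will be judged against. The abstract is the only place that states that figure directly. A trial that stopped at 63 families would satisfy the Sample size section, yet look 50% short of the abstract. A trial that enrolled 126 families would be twice as large as its own calculation supports, with a power that is stated nowhere.

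Workload doubles as well. The intervention has eight sessions (six plus two boosters), and the Potential Bias section has a single nurse delivering all of them. Assuming sessions are held per family, that is about 31.5 × 8 = 252 sessions under one target and 63 × 8 = 504 under the other.

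**Working it through.** **Inputs.** From Sample size: difference 6 points, SD 12, significance level 5% (taken as two-sided, which the article does not state), power 80%, ICC 0.05, baseline-endpoint correlation 0.5, attrition 20%. From Trial Participants and Sample size: two people per family.

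**Reproducing the plan's figures**

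1. Standardised difference: 6/12 = 0.5. A two-sample t-test needs 64 per arm. (The normal approximation, 2 × [12 × (1.960 + 0.842)/6]², gives 62.8.)
2. Baseline adjustment: factor 1 − 0.5² = 0.75, so 64 × 0.75 = 48 per arm.
3. Clustering: design effect 1 + (2 − 1) × 0.05 = 1.05, so 48 × 1.05 = 50.4 per arm. Rounded up, this is 51 per arm, or 102 individuals, as printed.
4. Attrition: 2 × 50.4 = 100.8 individuals, and 100.8/0.8 = 126.0 individuals, as printed. Starting from the rounded 102 gives 102/0.8 = 127.5, a small rounding difference.

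The 126 is therefore a count of individuals, and 63 per group is 126 individuals split 1:1.

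**Converting both targets to the same units**

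- Sample size section: 126/2 = 63 families, or 31.5 per arm.
- Abstract: 126 × 2 = 252 individuals, or 63 families per arm.
- Ratio: 252/126 = 2.

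**What each target delivers.** Effective n per arm is the analysed n divided by 1.05 × 0.75 = 0.7875. Power is from the noncentral t. The detectable difference at 80% power, by normal approximation, is (1.960 + 0.842) × 12 × √0.7875 × √(2/n).

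| | 126 individuals | 126 families |
|---|---|---|
| Families randomised | 63 | 126 |
| Individuals analysed after 20% attrition | 100.8 | 201.6 |
| Analysed per arm | 50.4 | 100.8 |
| Effective n per arm | 64 | 128 |
| Power for 6 points | 80.1% | 97.9% |
| Difference detectable with 80% power | 5.9 points | 4.2 points |

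The normal approximation gives power of 80.7% and 97.9%. On the t basis, the detectable difference in the first column is about 6.0 points.

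**Sensitivity to the ICC.** If the within-family ICC were 0.3 instead of 0.05 (an illustrative assumption), the design effect would be 1.30. Power by normal approximation would then be about 72% with 63 families and about 95% with 126.

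**The case against.** The strongest reply is that the Sample size section is coherent. It works in individuals throughout, states every input, converts 102 individuals to 51 families, and its figures reproduce. On that view the size and power of the trial are defined, and the abstract merely contains a slip of unit. Either target also gives at least about 80% power under the stated assumptions, so neither leaves the trial underpowered or changes the analysis.

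Much of this is fair. A slip in the abstract is the most likely explanation, and the calculation needs no repair beyond, at most, rounding. Two details should also be granted: the figure of 63 families is not printed but follows from two people per family, and the printed 102 leads to 127.5, so 126 is reached only by carrying the unrounded 50.4 per arm through the attrition step.

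None of this removes the contradiction. Both statements cannot be true, and nothing in the article says which one governs. A statistical analysis plan or fuller protocol could say which was meant, but could not make both right. Adequate power under either reading does not settle when recruitment ends or what a shortfall would be.

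**Conclusion.** The concern holds. The two stated targets differ exactly twofold, 252 individuals against 126, and the article does not reconcile them. The stated inputs support 126 individuals, that is 63 families, with about 80% power for 6 points. The abstract's 126 families would give about 98% power, or 80% power for about 4.2 points.

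This rests on two people per family, which the article states, and on a two-sided 5% test, which it does not. The power figures also take the ICC of 0.05, the correlation of 0.5 and the 20% attrition as given, with analysed families kept as pairs. The twofold discrepancy itself depends only on the family definition. Because it affects the headline sample size, it must be corrected.

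**What to change.** State one target, in families and in individuals, in both the abstract and the Sample size section.

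- **If the calculation stands:** change the abstract to 63 families (126 individuals; about 31 or 32 families per arm), and add the number of families beside the 126 individuals in Sample size. This is a one-line correction in each place and needs no extra participants. If the authors prefer to inflate from the rounded 102, 127.5 rounds up to 128 individuals, or 64 families (32 per arm); that choice should then be used throughout.
- **If 126 families were intended:** rewrite the Sample size paragraph for 252 individuals randomised and about 202 analysed, and state the resulting power (about 98% for 6 points) or the smaller difference targeted (about 4.2 points at 80% power). This costs more than wording, because recruitment and the nurse's caseload would be twice what the present calculation supports and would need justification.

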**Discussion:**

Depression both for patients and their carers is common after stroke. Our Depression Recognition and Treatment package (DepReT-stroke) may help clinicians be more effective at detecting and managing a common co-morbidity that limits rehabilitation and recovery.

**Trial Registration:**

ISRCTN: ISRCTN32451749

Research Ethics Committee Reference Number: 10/H0310/23

Grant Reference Number: (NIHR) PB-PG-0808-17056

## Background

### Stroke and depression

Stroke is a leading cause of disability, requiring considerable adjustment in the lives of those affected. Depression after stroke (Post Stroke Depression, PSD) is common and, compared with non-depressed stroke patients, is associated with worse long-term outcomes [1-3]. Depression is a distressing illness and is associated with a substantial reduction in quality of life and increased risk of suicide [4-6]. PSD occurs in up to 50% of all stroke survivors [7,8] with prevalence peaking approximately six months after the vascular event^9^. PSD is often inadequately diagnosed and treated, despite an evidence base for effective treatments [9]. Adherence with treatment is often poor, especially when prescribed without taking patient preferences into account. In England, stroke results in an estimated total annual cost of £7 billion [10,11].

### Treatment for depression

There is established efficacy for a range of treatments for depression that include medication, psychological treatments (such as cognitive behavioural therapy (CBT)) and exercise [12]. Antidepressants are effective in PSD both in terms of improving mood and enhancing stroke recovery [8,13]. Problems with the pharmacological treatment of depression seen in the general population are mirrored in patients with stroke. This includes inadequate prescriptions in terms of dose and duration [14,15] and treatment non-adherence: 44% within 3 months of starting treatment [16]. Generally patients express a preference for psychological over pharmacological treatments[17]. Cognitive Behaviour Therapy (CBT) with its problem-focused approach may be particularly suited to the treatment of PSD [18] being as effective as medication with about 50% of patients experiencing clinically meaningful improvement [19]. CBT is the treatment of choice for mild depression and is also recommended for moderate to severe depression or where patients refuse antidepressant treatment. Population studies have shown clear associations between physical exercise and mental health in older adults [20]. Recent trials in patients with PSD have shown exercise to be a feasible intervention that can significantly improve the patient's Activities of Daily Living and perceived physical health as well as help relieve depressive symptoms [20-23].

### The impact of stroke on carers

Many stroke survivors can live in the community, provided they have support and are cared for by a family member [24]. Care giving to a family member who has survived a stroke is demanding [25,26] and is associated with an increased risk of depression in the carer [27]. Patients' poor motor function, impaired memory and behaviour changes seem to have the most profound impact on carers' mental health [26-28]. Three months after the stroke up to 40% of carers will experience a depression, without a noticeable reduction in the prevalence 12 to 18 months after the event [27,29], with some evidence suggesting that care givers were in fact more likely to be depressed than the stroke sufferers themselves [27].

### Study rationale

The mental health of carers is intertwined with the mental health and disease presentation of stroke patients. Literature reviews suggest that stroke rehabilitation should focus on the family rather than the patient alone [30,31]. Stroke survivors whose families act as partners in the rehabilitation process achieve better outcomes [32] and spouses of stroke survivors can benefit significantly in physical and mental well being from nurse-led support and education programmes [33]. Therefore, working with families, rather than patients alone, may have an important role to play in enhancing the mental wellbeing of both group.

While effective management of PSD enhances stroke recovery and improves outcomes [34,35], PSD is often not recognised [35] and consequently treatment is not given. The Healthcare Commission [36] reports that following discharge from hospital, fewer than 30% of stroke patients with emotional problems (such as depression and crying) state they 'get enough help' from the NHS.

We aim to maximise the effectiveness of otherwise established depression treatments in stroke patients and/or carers by enabling them to make informed choices when selecting their depression treatment (i.e. medication, psychological treatments and exercise) and by continuing to support them in structured (adherence) sessions with a trained nurse conducted in their home. The participants' experience of the treatment package will be explored by semi-structured interviews with people with stroke, carers and involved health professionals to understand which aspects of the package are seen as most/least helpful and uncovering any potential barriers to routine use in the health service. This pragmatic approach will yield a much needed evidence based intervention that tests the efficacy mechanism for the prevention, recognition and treatment of depression in families after stroke [37].

The project will enable us to develop a package that will equip nurses (and other health workers) in the community to work effectively and productively in addressing the burden of depression in people with stroke and their carers. Tackling the burden of depression in families after stroke may help ensure optimal disease management leading ultimately to improved health and quality of life for people with stroke and their carers. An economic evaluation of the intervention will help us determine whether the intervention represents a cost-effective use of scarce NHS resources.

## Methods/design

### Trial objectives

To evaluate whether families who receive a Depression Recognition and Treatment package (DepReT-Stroke) in addition to treatment as usual (TAU), show improved mental wellbeing compared to those who receive TAU.

Secondary objectives are to evaluate whether families who receive DepReT-Stroke show improvements in mood, knowledge about depression, adherence to treatment and reduced carer burden compared to families receiving TAU; the process experience of DepReT-Stroke from the point of view of people with stroke, their carers and nurses delivering the intervention; the cost effectiveness of DepReT-Stroke in comparison to TAU.

### Summary of trial design

A single-blind, randomised controlled, cluster trial design to compare DepReT-Stroke with TAU in the treatment of depression in families living with stroke.

### Primary and Secondary Outcome measures

The primary outcome for DepReT-Stroke is change in the mental wellbeing of both patients and carers as measured by the Mental Component Summary (MCS) score of the Medical Outcome Study (MOS) 36 Item Short Form Health Survey (SF-36) version 2.

Secondary outcome measures for both the patient and their primary carer comprise: Hospital Anxiety & Depression Scale (HADS); Knowledge about Depression and Mania Inventory (KDMI); Beliefs about Medicines Questionnaire (BMQ); Zarit Carer Burden Inventory (ZCBI) (only to be completed by the carer); EuroQol quality of life questionnaire (EQ-5D); Levels of resource use associated with DepReT-Stroke and TAU

### Trial Participants

The study population are families living with stroke that have co-occurring depression in the patient, the carer or both. We will recruit 'families' (defined as a person suffering from stroke and their self declared primary carer) from the Norfolk and Norwich University Hospitals (NNUH) NHS Trust Stroke Register [38].

### Inclusion Criteria

The inclusion criteria for DepReT-Stroke are patients diagnosed with ischaemic or haemorrhagic stroke, confirmed by computerised tomography and listed on the NNUH stroke register; three months post stroke; living at home for not less than two weeks; has a self defined 'primary carer'; patient and/or carer scores ≥8 on the HADS; over 18 years of age (no upper age limit).

At three month post stroke the potential complications arising from the acute event should have settled and the patient is more likely to be relatively stable, both medically and psychologically. We chose at least two weeks post discharge from hospital/rehabilitation unit because it can be expected that a sense of routine is beginning to be established by the family by this time. According to the Healthcare Commission's report [36] patients '...can feel abandoned when they lose the emotional and practical support they receive in hospital...' Once patients have settled at home, they, and their families, may welcome further contact with specialist stoke staff.

### Exclusion Criteria

Families living with stroke will not be included in the trial if either the patient or the carer has a serious or unstable medical condition (e.g. advanced/incurable cancer; severe co-morbidity or severe unpredictable pain); psychosis or other severe mental illness; suicidal thoughts or ideation or dementia. We will also exclude families if either the patient or carer is institutionalised (e.g. care home resident) or is participating in any other research concerning stroke or depression

### Screening

The NNUH Stroke Register from 1^st ^January 2005 will be cross referenced with the hospital Patient Administration System (PAS) records to exclude patients who have subsequently died, have evidence of serious/unstable medical conditions or severe mental illness or as far as we can tell are not eligible to be included in the study for any other reason (i.e. discharge destination of residential or nursing home). A further screen for mortality will be conducted by telephoning the patient's GP to request information on their status. The remaining patients and their carers will be written to by the Consultant Stroke Physician who treated them whilst they were in hospital to invite them to participate in the study. The letter contains brief information about the trial, what it involves and includes a check list on the essential inclusion criteria (i.e. that the patient has a self-defined 'primary carer' and that either the patient and/or carer consider they are depressed [39]). If the patient and carer are interested in the study, they will be asked to complete a reply slip and send it back to the patient's consultant in the free post envelope provided. The reply slip requests information on the name of the person who wishes to be contacted by the research team and whether the patient has any difficulties with speaking.

Potential participants/carers will be telephoned by a research nurse who will make further enquiries on trial eligibility and administer the HADS questionnaire to the patient and/or carer as appropriate. If either the patient or carer has a HADS score ≥8 and they still wish to participate in the trial, the nurse will arrange a date for a Research Associate (RA) from the study team to visit them at home. All those approached will be asked whether they wish to receive written information about recognising, preventing and treating depression.

### Informed Consent

A research assistant from the study team will visit the family and make a final check on trial eligibility. Written and verbal versions of a Participant Information Leaflet (PIL) will then be presented to the person with stroke and their carer detailing the exact nature of the study. In particular the RA will explain the randomised allocation element of the trial. It will be made clear that the family is free to withdraw from the study at any time for any reason without prejudice to future care, and with no obligation to give the reason for withdrawal. The patient and carer will be allowed as much time as they wish to consider the information and ask questions. If required, the RA will facilitate opportunities to question other members of the research team, their General Practitioner (GP) or other independent parties to decide whether they will participate in the study. This may mean that the RA has to arrange a subsequent home visit at a later date after prior agreement and arrangement with the patient and the carer.

We will seek consent from the person with stroke whenever possible. An additional PIL has been designed to accommodate people with aphasia and the RA will be trained in effective strategies for communication with this patient group. Written Informed Consent will be obtained from the person with stroke and their carer if they were eligible and agreed to participate. In case of mental incapacity to give informed consent, we will seek approval of an appropriate personal consultee (which we expect will be the carer in most instances). Written information will be provided to potential consultees describing this role under section 32 of the Mental Capacity Act [40] and information about the research similar to that given to participants able to consent for themselves.

### Baseline measures

The RA who is masked to treatment allocation and trained to administer questionnaires in a standardised way will collect baseline data after informed consent is obtained. The following data will be collected:

#### Mental Component Summary of the 36 Item Short Form Health Survey (SF-36v2)

The SF36 is a self-report multidimensional measure of health-related quality of life and wellbeing [41]. The psychometric properties of the SF36 have been well established. The scales of the SF-36v2 address eight health domains and two summary measures are provided: a physical component summary score (PCS), and a mental component summary score (MCS). The MCS was selected as the main quality of life (QoL) outcome measure for this trial as it has been shown to have good sensitivity to change [42]

